## Abstract

**Background:**

Hypertension affects about 10 % of pregnancies and is responsible for both maternal and neonatal devastating complications such as eclampsia, HELLP syndrome, prematurity and maternal and neonatal death. The resolution of the disease occurs in the first twelve weeks postpartum. The behavior of blood pressure and occurrence of very high blood pressure episodes among women with severe preeclampsia is related to remodeling of the dynamics of body fluids with consequent increase in intravascular volume. The persistence of hypertension in critical levels results in increased puerperal morbidity.

**Objectives:**

To evaluate the effectiveness of furosemide in accelerating blood pressure recovery among women with severe preeclampsia.

**Methods/design:**

A triple-masked placebo controlled clinical trial, will be conducted including 120 postpartum women with severe preeclampsia, after eclampsia prophylaxis with magnesium sulfate and with adequate diuresis. Women with chronic hypertension and users of diuretics will be deleted. Informed consent will be obtained from all participants. Patients will be randomized to receive furosemide (40 mg orally every twenty four hours) or placebo. The variables are systolic and diastolic blood pressure, frequency of hypertensive crises, need for maintenance of antihypertensive therapy, number of antihypertensive agents used to control blood pressure, urine output, length of hospital stay, adverse effects and maternal complications. This study was approved by the Research Ethics Committee in humans of our institution. All participants will be duly informed about the aims of the project and will be included only if they agree to participate voluntarily, signing the informed consent.

**Trial registration:**

This study was registered on Clinical Trials.gov under the number NCT02163655. (http://clinicaltrials.gov/show/NCT02163655).

## Introduction

Hypertension in pregnancy continues to represent a real public health issue. Affecting 10 % of all pregnancies [1], hypertension is the first cause of maternal death in Brazil http://inseer.ibict.br/rbsp/index.php/rbsp/article/viewFile/474/pdf_150 and the second cause in the world [2, 3]. Worldwide, more than 99 % of cases of maternal deaths related to hypertension occur in low-income countries, reflecting not only a higher incidence as the lack of prenatal care and adequate treatment of obstetric emergencies [2]. Moreover, it is an important potentially life-threatening condition of life and cause of maternal near miss [4], along with increased perinatal morbidity and mortality [2]. It is also associated with long-term complications, with increased risk of cardiovascular disease in affected women [5, 6].

Among hypertensive disorders complicating pregnancy, pre-eclampsia and eclampsia represent the most severe conditions [7, 8]. Associated maternal risks include abruptio placentae, convulsions, acute pulmonary edema, convulsions, acute kidney injury and death. Perinatal risks are due to the reduction in the utero-placental blood flow and are represented by fetal growth restriction, hypoxia and fetal death, prematurity and its complications, among which the most important is the respiratory distress syndrome of the newborn [9].

It is well known that magnesium sulfate is the most effective and safe drug for preventing and treating eclamptic seizures and should be administered to all women in whom there is concern about eclampsia or eclampsia risk [10–14]. Magnesium sulfate significantly reduces maternal death when used to treat eclampsia and is a real "evidence-based solution" http://www.engenderhealth.org/files/pubs/maternal-health/engenderhealth-eclampsia-report.pdf. The only definitive treatment is delivery, and the resolution of pregnancy is indicated in all cases of eclampsia regardless of gestational age [9] in cases of preeclampsia at ≥ 34 weeks [9, 15, 16] and mild preeclampsia cases without other complications at ≥ 37 weeks [17].

However, even after birth and with appropriate treatment, concern about the complications of disease persist, since this condition can take days or weeks to resolve. In the postnatal period, with the return of liquid from the interstitial and extravascular compartment to the intravascular, very high blood pressure episodes are common and the persistence of hypertension in critical levels results in increased puerperal morbidity. Thus, blood pressure levels may continue to rise, which most often occurs in the first five days after birth, reaching a peak between three to six days after delivery [18]. New onset postpartum hypertension and preeclampsia can occur, with a frequency ranging from 0,3 %-27,5 % [19]. Complications of severe hypertension include stroke, eclampsia, congestive heart failure, acute pulmonary edema, renal failure and death [20].

Besides the mobilization of liquid from the interstiticial and intravascular to extravascular space corresponding to six to eight liters of the total body water, there is also a return of 950 mEq of total body sodium accumulated during pregnancy. It is observed increased urinary sodium excretion between three and five days after birth [21] possibly due to the increase of atrial natriuretic peptide in the first week after delivery, which has a role in natriuresis and entails inhibition of aldosterone, angiotensin II and vasopressin [22]. Several approaches have been proposed to accelerate the postpartum maternal recovery, but the effectiveness of these approaches as well as the ideal antihypertensive treatment in the postpartum period, remain to be established. Furosemide use has been proposed with this goal. Patients with preeclampsia and eclampsia may experience persistent hypertension after delivery, in response to the mobilization of interstitial and extravascular fluid into the intravascular space, the excess of total body water and inadequate secretion of sodium due to reduced glomerular filtration [23]. This is an important rationale for furosemide therapy since by its mechanism of action, this loop diuretic can act in patients with fluid overload, eliminating the intravascular fluid that has been mobilized in the postpartum period and thereby reducing blood volume and blood pressure and also reducing the need of antihypertensive therapy [23]. This therapy is logical when considering the pathophysiology of postpartum hypertension, with the objective of maintain a low central venous pressure and pulmonary capillary wedge pressures, raising colloid osmotic pressure and preventing the development of pulmonary edema and congestive heart failure [24].

In the systematic Cochrane Review that evaluated prevention and treatment of postpartum hypertension were included nine randomized clinical trials, of which two trials (282 women included) assessed postnatal furosemide at a dosage of 20-40 mg orally daily), compared with placebo or no treatment [25]. One trial added potassium supplementation (20 mEq orally daily) [23] and in the other [26] women at “high risk” of eclampsia also received magnesium sulfate. None of the studies reported the mean and standard deviation of the baseline blood pressure but one trial [26] reported a greater decrease in blood pressure in the group receiving furosemide compared to placebo. In the group receiving furosemide it was reported a change of blood pressure on days one, three and seven after delivery (i.e., −6.5 mmHg (furosemide) versus −3.5 (placebo) on day one, −10.6 (furosemide) versus −9.75 (placebo) on day three, and −11.5 (furosemide) versus −7.8 (placebo) on day seven). In the other trial [23] including 264 women, only postpartum patients with severe preeclampsia (*n* = 70) who received furosemide compared with controls had significantly lower systolic blood pressure by postpartum day 2 (142 +/− 13 mmHg compared with 153+/−19 mmHg, *P* < .004) and required less antihypertensive therapy during hospitalization (14 % compared with 26 %, *p* = 0.371) and at discharge (6 % compared with 26 %, *P* = 0.045). Follow-up ranged from day 10 postpartum [23] to six weeks postpartum [26].

The reviewers conclude that reliable data are not available to guide management of women with postpartum hypertension. For women with pre-eclampsia, postnatal furosemide may decrease the need for postnatal antihypertensive therapy in hospital, but more data are needed on substantive outcomes before this practice can be recommended. Notwithstanding, the optimal management of postpartum hypertension is not yet well established.

Thus, to determine the potential benefit of using diuretics in women with preeclampsia is an important issue in modern obstetrics. This study will be carried out with the objective of determining the effectiveness of furosemide to accelerate the recovery of hypertension in postpartum patients with severe preeclampsia.

## Objectives and hypothesis

The overall objective is to determine the effectiveness of furosemide to accelerate the recovery of hypertension in postpartum patients with severe preeclampsia in a randomized clinical trial.

The hypothesis is that mean daily average systolic, diastolic and mean arterial pressure (MAP) and the frequency of very high blood pressure episodes when furosemide is administered is lower.

### Specific objectives

In patients with severe preeclampsia receiving furosemide or placebo in postpartum, compare:

## Primary outcomes

Daily average of systolic, diastolic and mean arterial pressure (MAP);Heart rate;Frequency of very high blood pressure episodes.

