### Main hypothesis

In women randomized to postpartum oral furosemide, in comparison to placebo:Daily averages of systolic, diastolic and mean arterial pressure (MAP) are lower, heart rate is the same and the frequency of very high blood pressure episodes is lower.Control of blood pressure is obtained earlier;Frequency of use of antihypertensive agent for the treatment of hypertensive crisis is lower, as well as the need for maintenance of antihypertensive therapy for blood pressure control;Fewer antihypertensive agents are needed in order to control blood pressure at hospital discharge;Time until blood pressure control is lower;Daily urine output is higher;Reduction of edema is obtained in less time;Length of hospital stay is reduced.

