### Procedures for selecting participants and randomization

Eligible patients in labor will be invited to participate and those who agree and sign the informed consent form will be included in the study and then will be allocated to either using furosemide or placebo according to a random list of numbers generated by the Random Allocation Software Ispharan Iran, version 1.0. This list of randomization will be provided by the statistician to the pharmacist who will be responsible for preparing the packages containing either the furosemide or placebo, both in an identical presentation, with the identification number of list labeled. This procedure will be followed in order to guarantee the concealment of allocation of patients in both arms. Both patients and medical staff should be blind of the intervention condition in each case. Study medication and placebo, after delivered by the pharmaceutical industry to the pharmacy, will be packed as previously described and according the random list. The pharmacy will be responsible for sending sets to the ICU were the nurse in charge will keep all the packages until the administration of the drug to the patient according to the patients’ enrollment. The subjects will receive the study medication every 24 hours for a maximum of five days.

During the observation period the women will be subject to strict control of blood pressure, urine output (diuresis evaluated spontaneous or urinary catheter) and weight control. The routine management adopted at the hospital will be followed and other hypertensive agents will be initiated and chose according to the attending clinician's discretion.

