### Main outcomes

Systolic blood pressure (SBP): Determined by the appearance of the first sound of Korotkoff. Continuous quantitative variable, expressed in millimeters of mercury (mmHg).Diastolic Blood Pressure (DBP): Determined by the appearance of the fifth Korotkoff sound. Continuous quantitative variable, expressed in millimeters of mercury (mmHg).Mean arterial pressure (MAP): The value of mean arterial pressure in mmHg. Will be calculated by the formula: systolic blood pressure (SBP) plus twice the diastolic blood pressure (DBP) divided by three, being represented by (+2PAD SBP)/3. Continuous quantitative variable, expressed in millimeters of mercury (mmHg).Heart rate: Refers to the number of heart beats per minute, measured at least four times daily.Frequency of very high blood episodes: Defined as the daily number of very high blood pressure episodes, defined as Systolic blood pressure ≥ 180 mmHg or Diastolic blood pressure ≥ 110 mmHg.Control of blood pressure: Defined < 140 mmHg of systolic blood pressure and < 90 mmHg of diastolic blood pressure at all measurements (at least four) for a minimum 24-hour.Need for maintenance of antihypertensive therapy for blood pressure control: Use of anti-hypertensive agents for blood pressure control.Number of antihypertensive agents used to control blood pressure: Number of antihypertensive agents used to control blood pressure.Time required for recovery of blood pressure: Time to achieve control of blood pressure expressed in whole numbers.Hospital stay: For time elapsed between the beginning of inpatient treatment with furosemide or placebo until discharge.Daily urine output: Defined as the average amount of urine excreted, expressed in milliliters (ml), collected by probe or spontaneous voiding during hospitalization.

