**Fig. 1 Fig1:**
[figure not shown]
Study design and population (CONSORT, 2010) [27]

The characteristics of the participants in each group will be compared with Student’s *t* test for continuous variables with normal distribution and Mann–Whitney U test for discrete and ordinal variables or those with non-normal distribution. Categorical variables will be compared with Pearson’s χ [2] test or Fisher’s exact test, as appropriate. P values for all tests will be two tailed at a 5 % level of significance.

Risk ratios and their 95 % confidence intervals will be calculated as a measure of relative risk. The number needed to treat (NNT) and its 95 % confidence interval will be calculated for the outcomes in which a beneficial effect of using furosemide is achieved, using the EBM calculator [http://moosenose.com/EBCalculator.htm]; in case of adverse effects the number needed to harm (NNH) and its 95 % confidence will also be calculated.

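### Five unranked primary outcomes, each tested at two-sided 5 %, have no decision rule, and the stated 90 % power covers systolic pressure alone

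*Protocol article*

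**What the plan says.** - **Primary outcomes:** "Daily average of systolic, diastolic and mean arterial pressure (MAP);Heart rate;Frequency of very high blood pressure episodes". That is five outcomes: systolic pressure (SBP), diastolic pressure (DBP), mean arterial pressure (MAP), heart rate and very high pressure episodes. None is marked as decisive.
- **Main hypothesis:** "Daily averages of systolic, diastolic and mean arterial pressure (MAP) are lower, heart rate is the same and the frequency of very high blood pressure". The sentence goes on to predict that such episodes are fewer. Four outcomes are therefore expected to fall and one to show no difference. The hypothesis under Objectives and hypothesis names the same four and leaves heart rate out.
- **Time:** the pressures are daily averages. The episode outcome is "Defined as the daily number of very high blood pressure episodes". On duration: "The subjects will receive the study medication every 24 hours for a maximum of five days". No day, and no summary over days, is singled out. The Dependent variables section lists daily maximum pressures instead of averages.
- **Data analysis plan:** "P values for all tests will be two tailed at a 5 % level of significance". No decision rule (any or all) and no adjustment for several primary outcomes is given.
- **Sample size calculation:** one contrast, SBP 142 (SD 13) v 153 (SD 19) mmHg, at 90 % power and 5 % significance, giving 94 patients, or 120 after allowing for 20 % losses. The Introduction shows where the contrast comes from: in an earlier trial, women with severe preeclampsia on furosemide "had significantly lower systolic blood pressure by postpartum day 2". No effect or power is assumed for the other four primary outcomes.

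**The concern.** A trial with several primary outcomes needs a rule saying which result, or how many, decides that the treatment works. Without one, the 5 % and the 90 % cannot be attached to the trial's conclusion, because each depends on the rule.

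- If one significant outcome is enough, each extra outcome tested at the full 5 % adds a chance of a false positive.
- If all must be significant, the error rate is safe, but power is at most that of the weakest outcome, and only SBP has been given any.

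At stake is the main conclusion. As the plan stands, a lone significant result on any primary pressure outcome could be presented as a positive trial, and a rule chosen after unblinding would not be credible.

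**Working it through.** **Inputs from the protocol article:** means 142 and 153 mmHg (difference 11), SDs 13 and 19, power 90 %, two-sided 5 %, losses 20 %, and MAP = (SBP + 2 × DBP)/3.

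**Assumptions, because the article gives no figures:** 1:1 allocation; correlation of SBP with DBP 0.5 to 0.8; correlation of episodes with either pressure 0.3 to 0.7; SD of DBP 11 mmHg, used only to weight MAP; episodes treated as approximately normal.

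**1. The stated sample size.** n per arm = (1.960 + 1.2816)² × (13² + 19²)/11² = 10.507 × 530/121 = 46.02, rounded up to 47, so 94 in total. This reproduces the article. With losses, 94/0.80 = 117.5, or 118, close to the stated 120. Power at 47 per arm: 11/√(530/47) = 3.276, and Φ(3.276 − 1.960) = 90.6 %. This is the power of one SBP test at 5 %.

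**2. If any one of the four directional outcomes is enough, at a single time.** If independent, the two-sided error is 1 − 0.95⁴ = 18.5 %. In the favourable direction it is 1 − 0.975⁴ = 9.6 %, against a nominal 2.5 %. Independence overstates this, because MAP is computed from SBP and DBP. Simulation under no effect gives:

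| SBP–DBP correlation | Episodes–pressure correlation | At least one p < 0.05, two-sided | At least one in favour of furosemide |
|---|---|---|---|
| 0.5 | 0.3 | 13.8 % | 6.9 % |
| 0.7 | 0.5 | 12.2 % | 6.1 % |
| 0.8 | 0.7 | 10.6 % | 5.3 % |

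**3. If all must succeed.** The error rate is at or below 5 %. Joint power cannot exceed that of the weakest outcome. As an illustration only, four independent outcomes with 90 % power each would give 0.9⁴ = 65.6 %. Positive correlation would raise this. The article has no inputs from which to calculate the true figure.

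**4. Keeping the four as alternatives with a Bonferroni split.** Each is tested at 0.05/4 = 0.0125, critical value 2.498. SBP power at 94 evaluable is Φ(3.276 − 2.498) = 78.2 %, and 88.6 % if all 120 are evaluable. To restore 90 %: (2.498 + 1.2816)² × 530/121 = 62.6, so 63 per arm, 126 evaluable and 158 with losses (126/0.80 = 157.5).

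**5. One SBP primary outcome.** Step 1 applies unchanged: 94 evaluable, 120 enrolled.

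**The case against.** The strongest defence is that the hypothesis is worded as a conjunction: SBP, DBP, MAP and episodes are all to be lower. Read as a decision rule, that controls the error rate. Moreover, the article condenses a fuller protocol, and an analysis plan that is not shown may set the rule, the day and any adjustment. This stands in part: an any-one rule is nowhere stated, so the inflation is conditional on it. It does not remove the point. The article itself fixes five co-equal primary outcomes, gives every test the full 5 % and sizes the trial on one of them. Under the conjunction, the 90 % would cover only one of its four parts.

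A reader might also infer more than the text supports:

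- **That both the 5 % and the 90 % fail together.** No single rule does this. Under an any-one rule the SBP test keeps its power; under an all rule the error rate is controlled.
- **That there are 25 primary tests (five outcomes on five days).** The article does not say each day is tested separately, and daily averages could feed one summary per woman. If each day were tested, the error would be higher: for the 20 directional tests, 64.2 % if independent and about 21 to 44 % with day-to-day correlation from 0.9 to 0.5. That is an upper reading only.
- **That heart rate is a fifth route to success.** A significant difference would contradict the hypothesis. Nor would a non-significant test show that heart rate is the same.
- **That the sized quantity is SBP on treatment day 2.** The reference value is from postpartum day 2. Treatment here follows completion of magnesium sulfate, so the two days need not coincide.
- **That the eleven variables under Main outcomes are all primary.** That section defines variables, and the article separates primary from secondary elsewhere.

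**Conclusion.** The point holds in a limited form. The protocol article leaves open which of five primary outcomes decides the trial, and when, while testing each at two-sided 5 %. The sample size arithmetic is correct, but for one SBP comparison only.

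For four directional outcomes at one time, an any-one rule at least doubles the nominal error on every correlation tried: about 11 to 14 % against 5 % two-sided, and about 5 to 7 % against 2.5 % in the favourable direction. Under an all rule there is no inflation, and the gap is in power, which is unknown for everything except SBP.

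The error figures rest on the assumed correlations. The counts of outcomes, the 5 % for every test and the single sizing contrast do not. It should be settled before unblinding because it concerns the trial's main conclusion and cannot be credibly repaired afterwards.

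**What to change.** Amend the wording before unblinding:

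- Name SBP as the single primary outcome, furosemide v placebo, at two-sided 5 %. Fix one time, or one summary over days, and say whether the daily value is an average or a maximum.
- State that 90 % power with 94 evaluable (120 enrolled) applies to that comparison. Note that the reference difference and SDs are from postpartum day 2, so for another time or summary they are an assumption.
- Make DBP, MAP and very high pressure episodes secondary. Test them in a stated fixed order after SBP, or report them without confirmatory claims.
- Move heart rate to a secondary or safety outcome, reported as a difference with a confidence interval.

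This needs no extra patients. The cost is that only SBP carries a confirmatory claim unless the ordered tests also succeed. Keeping the four directional outcomes as alternative routes to success is possible, but on a Bonferroni split it would need about 158 enrolled to keep 90 % power for SBP, and the other three would still need effect assumptions of their own.

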### Secondary maternal outcomes

Control of blood pressure;Frequency of use of antihypertensive agent for the treatment of hypertensive crisis;Need for maintenance of antihypertensive therapy for blood pressure control;Number of antihypertensive agents used to control blood pressure at hospital discharge;Time until blood pressure control;Daily urine output;Reduction of edema;Length of hospital stay;Adverse effects: hypokalemia, polydipsia, headaches, mental confusion, muscle aches, tetany, muscle weakness, heart rhythm disturbances and gastrointestinal symptoms;Frequency of maternal complications: imminent eclampsia, eclampsia, infection, bleeding manifestations, shock and maternal death.

